## Abstract

**Background:**

Utilization of total knee arthroplasty is increasing rapidly. A substantial number of total knee arthroplasty recipients have persistent pain after surgery. Our objective was to design a randomized controlled trial to establish the efficacy of a motivational-interviewing-based telephone intervention aimed at improving patient outcomes and satisfaction following total knee arthroplasty.

**Methods/Design:**

The study was conducted at Brigham and Women’s Hospital in Boston, Massachusetts. The study focused on individuals 40 years or older with a primary diagnosis of osteoarthritis who were scheduled for total knee arthroplasty. The study compared two management strategies over the first six months postoperatively: 1) enhanced postoperative care with frequent follow-up by a care navigator; 2) usual postoperative care. Those who were randomized into the enhanced postoperative care arm received ten calls from a trained non-clinician care navigator over the first six postoperative months. The navigator used motivational interviewing techniques to engage patients in discussions related to their rehabilitation goals, including patient’s plans for and confidence in achieving those goals. Patients in the usual care arm received standard postoperative management and received no navigator phone calls. Patients in both arms were assessed at baseline, three months, and six months postoperatively.

**Discussion:**

The primary outcome of the study was improvement in function as measured by the difference in Western Ontario and McMaster Universities Osteoarthritis Index function score between preoperative (baseline) status and six months postoperatively. Data were collected to identify factors that may be related to total knee arthroplasty outcomes, including preoperative pain, pain catastrophizing, self-efficacy, and depression. A formal economic analysis is also planned to determine the cost-effectiveness of the care navigator as a component of total knee arthroplasty care.

**Trial registration:**

ClinicalTrials.gov
NCT01540851

## Background

Total knee arthroplasty (TKA) is a frequently used procedure to reduce pain, improve functional status, and enhance quality of life in persons affected by advanced knee osteoarthritis (OA)
[1]. A growing body of evidence suggests that approximately 20% of TKA recipients have persistent knee pain following surgery
[2]. Greater preoperative levels of pain, functional limitation, medical comorbidity, depression, catastrophizing and lower self-efficacy have all been identified as potential risk factors for poor symptomatic and functional outcomes of TKA
[3-7].

Motivational interviewing (MI) is a client-centered, semi-directive method of engaging intrinsic motivation to change behavior. MI was developed in the context of substance abuse, but has since been applied to a variety of health problems ranging from unsafe sexual behavior to diabetes management
[8,9]. Rosal and colleagues designed a randomized trial to establish the efficacy of a theory-based telephone-delivered short Patient Self-Management Support intervention in post-TKA patients
[10]. The intervention was partially based on the principles of MI and concluded 9 weeks post-TKA. Functional outcomes were measured at 6 and 12 months post-TKA. The preliminary results presented at the Annual Meeting of the American Academy of Orthopedic Surgeons in 2012 did not show a substantial effect of the intervention on functional improvement. However, the rehabilitation process following TKA is rigorous and often takes longer than 8–9 weeks
[11]. We aim to build upon the Rosal trial by using an MI-based intervention, extending the intervention to 22 weeks and gathering additional data on adherence to the rehabilitative process, utilization of emergency departments, and satisfaction with the surgery.

The Adding Value in Knee Arthroplasty (AViKA) Postoperative Care Navigation Trial is a randomized controlled trial to assess the efficacy of an MI-based postoperative intervention, carried out by MI-trained researchers (“navigators”), on the functional recovery of patients undergoing primary unilateral TKA for OA.

## Methods/Design

The team considered retrospective vs. prospective data collection and observational vs. interventional designs. Retrospective studies are typically less costly and time-consuming than prospective studies. However, a retrospective design could not address our research question because the current standard of care practices for TKA patients does not include the motivational interviewing (MI) intervention we sought to evaluate. We considered using a single-arm study of a navigator-led intervention and comparing the results with historical controls or control patients at another institution. However, the processes of care for TKA recipients are evolving rapidly and are not uniform across centers. Thus, the contrast between intervention and control could be complicated by secular and institutional differences in the care process. Equally important, non-randomized designs do not ensure balance in patient characteristics across treatment arms.

The randomized controlled trial (RCT) overcomes these problems, but may introduce its own limitations. First, an RCT may lack external validity if a substantial number of patients refuse to participate, raising the question of whether the participants truly represent the population that the findings are intended to inform. However we discussed the RCT design with post-TKA patients in focus groups who indicated they would be comfortable with randomization in this setting. On the basis of all these considerations, we proceeded with a two-arm randomized controlled trial. To address the issue of external validity and generalizability, we collected basic demographic baseline data on patients who were eligible but chose not to participate.

Patients randomized to the navigator arm received an intervention based on MI principles with a focus on behavior change. Behavior change has been described using the Transtheoretical Model, which distinguishes six phases of change: pre-contemplation, contemplation, determination, action, maintenance, and relapse
[12,13]. The Adding Value in Knee Arthroplasty (AViKA) care navigator intervention is focused on behavior change in three domains: adherence to prescribed physical therapy, increased weekly physical activity, and achievement of patients’ personal goals for recovery.

### Setting and sample

#### Ethics statement

This study was approved by the Partners Healthcare Institutional Review Board (IRB) (protocol 2010P002597). Written consent was obtained from all participants in the AViKA Trial.

The AViKA Trial was conducted at Brigham and Women’s Hospital (BWH), a tertiary academic medical center in Boston, MA. The surgeons in the BWH Department of Orthopedic Surgery perform over 1,400 TKAs annually. Patients were recruited from the practices of five BWH orthopedic surgeons. To be eligible to participate in AViKA, patients needed to be 40 years of age or older, scheduled for a primary TKA at BWH, and have a diagnosis of degenerative knee OA. The full inclusion and exclusion criteria (including justifications for these criteria) are provided in Table 
1.

**Table 1 T1:** AViKA study inclusion and exclusion criteria

**Inclusion Criteria:**	**Exclusion Criteria:**
▪ Scheduled to undergo primary TKA at BWH	▪ Osteoarthritis is not the underlying diagnosis (e.g. inflammatory arthritis)
▪ Osteoarthritis is the principal underlying diagnosis	▪ Psychological issues that preclude participation, as identified by participating surgeons
▪ Age ≥ 40 years at the projected date of TKA	▪ Dementia
▪ English-speaking	
	▪ Non-English speaker
	▪ Age < 40 at the projected date of TKA
	▪ Lives in a nursing home (difficult to track costs)
	▪ Implantation of unicompartmental knee arthroplasty or interpositional arthroplasty (different clinical features and different costs)
	▪ Bilateral TKA (simultaneous, staged or planned within 6 months)

### Screening, enrollment, and randomization

#### Screening

Patient eligibility was assessed by a research assistant using two data sources, the Partners HealthCare Longitudinal Medical Record (LMR) and Electronic Surgical Plan (ESP). Upon confirming basic patient eligibility in LMR and ESP, operating surgeons were sent a confidential email listing potentially eligible patients and their date of surgery. Surgeons were asked to exclude patients with dementia or psychological issues that would preclude participation, patients with planned unicompartmental knee arthroplasty, interpositional arthroplasty, or bilateral (staged or simultaneous) TKA. Patients were considered to have passed the surgeon screen if the operating surgeon did not request exclusion from the study within three business days.

#### Enrollment

The Partners IRB required that a recruitment letter be sent to each patient before enrollment in the trial. The recruitment letter described the goals of the study, explained randomization and the intervention and detailed the payment plan for participants. Patients were informed that they would be called by the research assistant and invited to enroll in the study if they did not actively opt out prior to the enrollment call. Due to time constraints, patients with TKA scheduled within 28 days of the screening date were not eligible for recruitment unless the operating surgeon provided written confirmation that the study had been discussed during the clinic visit.

Patients who did not opt out of the study were contacted by a research assistant, who used a standardized script to provide a detailed description of the study. Patients who wished to participate were mailed an informed consent form and baseline questionnaire. The research assistant then met patients in person during their standard preoperative appointment (usually scheduled two weeks before surgery) to obtain written informed consent and collect the baseline questionnaire. For the first 9 months of the study the research assistant also performed a brief physical examination during the baseline visit that measured knee range of motion.

#### Randomization

After surgery, patients were randomized to one of the two treatment arms, enhanced postoperative care (navigator arm) or usual care. The randomization schedule was stored in a password protected file, accessible only to the study data manager ([name]). Patients were randomized by the data manager ([name]) the day after surgery in the order in which surgery was completed. We used randomly varying permutated blocks with varying block sizes to randomize patients within 8 strata. The strata included age (<65 vs. 65+), sex, and surgeon (high volume vs. low volume). Please refer to Figure 
1 for a visual representation of the two study arms.

**Figure 1 F1:**
[figure not shown]
**AViKA treatment arms.** This figure depicts the two treatment arms of the AViKA study: the care navigator arm and the usual care arm. Patients in both arms received questionnaires at baseline and post-operative months three and six. Patients in the care navigator arm also receive regular phone calls from the care navigator. The time points designated in parenthesis indicate the post-operative time point (that is, “Call from care navigator (*week 4*)” indicates that the care navigator called the patient one month after the date of the patient’s TKA).

### Interventions

#### Enhanced postoperative management (navigator arm)

Patients randomized to the navigator arm received ten calls over the six months following their surgery: weekly for the first postoperative month (weeks 1, 2, 3, 4), biweekly for months two and three (weeks 6, 8, 10), and monthly for months four through six (weeks 14, 18, 22). In accordance with the principles of MI, these calls had no set script or agenda; the navigators did not give instructions and only provided advice when asked. On each call, the objective of the navigator was to elicit information from the patient including: what goals the patient would like to achieve (short- and/or long-term, depending on the call), why the patient would like to achieve those goals (specifically, the benefits of the goal), how the patient planned to achieve the goals (specific strategies), any barriers or possible challenges the patient anticipated (including how the patient might deal with such challenges), and why the patient felt they would be able to achieve these goals. Navigators also encouraged and congratulated the patient’s achievements, gave the patient the opportunity to air frustrations and concerns, and used reflection and open-ended questions to affirm the patient’s experiences and progress. When appropriate, the navigators provided the patient with information and encouraged the patient to contact his or her surgeon, physical therapist, or other appropriate healthcare provider for medical concerns. Table 
2 provides a list of major techniques used by the navigators.

**Table 2 T2:** **Navigation techniques**: **example conversation excerpts**^*^

	
**Developing goals:**	
*Eliciting ambivalence*	“Getting to the gym has been very challenging now that you've returned to work! You mentioned that you would like to get to the gym more often – why is that?”
**Discussing established goals**	
*Confidence ruler*	“On a scale of 1 to 10, how confident are you that you can walk without a cane?”
	“Why did you rate yourself at [X] rather than a [lower number]?”
*Asking about potential barriers*	“What challenges do you anticipate as you start thinking about returning to golf?”
**Patient is discouraged and/****or did not achieve goal**	
*Affirmation and encouragement*	“I'm sorry to hear that you had to go to the hospital this week for pneumonia - I'm so glad you're feeling better! Despite the interruption to your recovery, it's wonderful that you achieved 108 degrees of flexion. Last time we spoke you were at 100 degrees – this is a huge improvement!”
**In response to clinical concerns**^ **+** ^	
*Referral to appropriate clinician*	“It sounds like you're dealing with a lot of swelling in the knee and want a sense of whether that is normal. Did you mention this to the physical therapist today? What did he/she have to say?”
	“You're having new sharp pains in the knee. Have you considered speaking your surgeon and his/her team? If you would like, I can provide you with the number.”
**Throughout conversation**	
*Asking permission*	“Do you mind if I ask why you originally decided to go through with the surgery?”
*Open-ended questions*	“Where would you like to see yourself one week from now?”; “How have your exercises been going the last few weeks?”
*Simple and complex reflection*	“It sounds like the flexion exercises are the most difficult for you and the pain is tremendous. At the same time, I'm hearing that you feel these are the most important for your recovery. Can you tell me more about the benefits of these exercises?”
*Summarization*	“I'm so happy to hear that since we last spoke your flexion has improved, and you've felt comfortable cutting back on the pain medications. It sounds like you feel ready for the transition to outpatient therapy. Swelling is still making improvement difficult for you, but icing and elevation have been helping, and you hope to continue that through the next week. I look forward to speaking with you next week and hearing how things go as you continue to practice your gait and try walking outside for the first time! Do you have any questions or anything else you'd like to discuss today?”

^*^All techniques, except “referral to appropriate clinician” were informed by the principles of motivational interviewing.

^+^Navigators were trained to recognize symptoms of serious adverse events (such as infection or pulmonary embolus), and were to instruct the patient to dial 911 in such cases.

Early navigator calls often focused on patient goals in relation to physical therapy (including adherence to the prescribed regimen, achievement of range-of-motion milestones, pain management through icing and medications), as well as short-term goals to return to the patient’s desired level of function (including household activities, improved mobility, and return to activities out of the home). As the patient moved along in recovery, focus often shifted toward patient’s longer-term goals for recovery (including athletic activities, participation in specific upcoming events, and commitment to regular physical activity). Table 
3 lists common goals at each stage of the recovery process.

**Table 3 T3:** **Common ****patient goals after total knee arthroplasty**^+^

	
**Weekly 1–4 (**** *postoperatively* ****)**	▪ Reduce pain, swelling; improve sleeping
	▪ Adhere to prescribed physical therapy routine
	▪ Improve range-of-motion (extension and flexion)
	▪ Move from walker → cane → no supportive device
	▪ Improve mobility; increase walking distance (getting out of the house, walking up and down stairs)
	▪ Reduce pain medications
**Weekly 6–10 (**** *postoperatively* ****)**	▪ Limit pain medications to evenings and before physical therapy sessions
	▪ Improve speed and stability of gait
	▪ Start driving again
	▪ Return to work
	▪ Walk up and down stairs “reciprocally” (“foot-over-foot”)
	▪ Improve range of motion (extension and flexion)
	▪ Fit physical therapy into increasingly busy routine
	▪ Increase time and comfort on stationary bicycle
	▪ Prepare for athletic goals (tennis, biking, walking, hiking, golf, etc.)
	▪ Return to regular daily walking, stretching, exercise routines
	▪ Adhere to prescribed physical therapy routine
**Weekly 14–22 (**** *postoperatively* ****)**	▪ Develop a regular routine that includes physical activity
	▪ Continue to strengthen leg muscles
	▪ Return to athletic activities (tennis, biking, walking, hiking, golf, etc.)
	▪ Manage co-morbid musculoskeletal conditions

^+^Each patient is unique and the trajectory of recovery can vary greatly; however, this table is intended to give a general sense of what many patients’ goals may be at different stages of recovery.

#### Navigator training

Prior to working with patients, care navigators studied the work on MI by its creators, Miller and Rollnick
[14], and received personal training and coaching in MI techniques by an expert in MI with doctoral training in behavioral science and clinical epidemiology. Navigators observed inpatient and outpatient care (including physical therapy and outpatient follow-up with the surgeon) specific to post-TKA patients.

#### Usual care arm

Patients randomized to the usual care arm completed the standard of care rehabilitation protocol offered by BWH for TKA recipients. Usual care consists of immediate active or active-assisted range of motion and progressive gait training during the hospital stay. The majority of patients are discharged home with a prescribed physical therapy regimen and later transition to outpatient physical therapy. Often patients receive some form of therapy three to six months after surgery, with the exact number of visits varying among patients.

### Outcome measures

The primary outcome of the study was the difference between the two arms in functional improvement from preoperative (baseline) status to six months postoperatively, as measured by the difference in Western Ontario and McMaster Universities Osteoarthritis Index (WOMAC) function score. Secondary outcomes included quality-of-life improvements (as measured by EuroQol) and health care services utilization over the course of three and six months postoperatively.

### Assessments

#### Timing

All study participants received their initial assessment at the time of preoperative visit, usually occurring within two weeks prior to the date of surgery. Study participants were also assessed at three months after surgery and at the time of primary outcome assessment, six months postoperatively. These assessments were done by self-reported questionnaires.

#### Blinding

The principle investigator and the team responsible for patient enrollment and assessment were blinded to the patients’ study group assignments. Un-blinding personnel only took place in emergency situations. If un-blinding needed to occur, the study coordinator noted the un-blinded patient’s identification number, reason for un-blinding, person responsible for un-blinding study staff, and the list of persons now un-blind to the patient’s treatment.

### Noncompliance and termination

A patient’s participation was considered complete if the patient completed all study assessments through the six month time point. Patients were terminated if they cancelled their TKA, underwent a contralateral TKA within six months of their index procedure, or if their surgeon requested their early termination. In the case of contralateral TKA, patients assigned to the navigator arm continued to be followed by the navigator until their contralateral TKA was performed.

If a patient requested withdrawal from the navigator arm they were invited to submit their three and six month questionnaires, enabling the research team to track outcomes of those who declined participation in the intervention arm over the course of the study. Patients who were unwilling to continue with the study protocol altogether were considered early withdrawals. Patients who requested withdrawal from the study were asked standardized questions regarding their reason(s) for withdrawal including cancellation of surgery, too sick, too busy, no longer interested, or other.

There were no additional evaluations for withdrawn patients. At the time of early withdrawal, premature termination, or study completion, the research assistant mailed the patient a study completion letter which documented their withdrawal and confirmed that this would not affect the medical care the patient received at BWH.

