### Analytic approach

The primary analysis will be a comparison of six month changes in WOMAC function score between the care navigator and the usual care groups, using the “intention to treat” approach, in which subjects are analyzed in the group to which they were randomly assigned. We will also perform a secondary “intention to treat” analysis in which the dependent variable is a failure indicator defined as failing to achieve a minimal clinically important improvement in WOMAC function score (one half of the standard deviation)
[15,16]. This analysis provides an estimate of efficacy at the level of the subject rather than the group. We will perform additional exploratory analyses to identify factors associated with outcome, including preoperative functional status and pain, catastrophizing, self-efficacy, and depression, as per prior literature
[3-7]. If the intervention is associated with improvements in functional outcome, we will use general linear models to determine whether intervention effects are mediated by improvements in self-efficacy or catastrophizing.

In addition, a formal economic analysis is planned to determine the cost-effectiveness of the care navigator intervention as compared with usual care. The analysis will incorporate accepted principles of cost-effectiveness analyses including a societal perspective and discounting of all costs and health benefits
[17].

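### Randomized patients with a contralateral TKA, or terminated at the surgeon's request, have no stated route to a six-month WOMAC, so intention to treat cannot rest on observed outcomes for everyone

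*Protocol article*

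**What the plan says.** Noncompliance and termination gives three triggers for ending a patient's participation: "Patients were terminated if they cancelled their TKA, underwent a contralateral TKA within six months of their index procedure, or if their surgeon requested" it. No criteria are given for a surgeon's request.

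The same section says: "There were no additional evaluations for withdrawn patients". It continues: "At the time of early withdrawal, premature termination, or study completion, the research assistant mailed the patient a study completion letter which documented their withdrawal". The one group explicitly asked for further data is a different one: "If a patient requested withdrawal from the navigator arm they were invited to submit their three and six month questionnaires". For contralateral surgery the section mentions only the navigator's contact: "patients assigned to the navigator arm continued to be followed by the navigator until their contralateral TKA was performed". It is silent on questionnaires after that operation.

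On timing, the Randomization section states: "After surgery, patients were randomized to one of the two treatment arms", and places this "the day after surgery in the order in which surgery was completed".

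The Analytic approach section makes the primary analysis an intention-to-treat comparison of six-month change in WOMAC function, "in which subjects are analyzed in the group to which they were randomly assigned".

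Table 1 excludes bilateral TKA at entry, whether simultaneous, staged or planned within six months.

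**The concern.** Cancelled surgery can only precede randomization, so that trigger does no harm to the comparison. The other two come after it. If they end data collection, some randomized patients have no primary outcome because of a rule in the protocol, not because they chose to stop. An analysis plan can model or impute such a score, but it cannot recover one that was never requested.

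The loss may also be informative. A second knee operation may depend on how recovery from the first is going, and recovery is what the intervention targets. Navigators encouraged patients to contact their surgeon about medical concerns, and this happened in one arm only. The Blinding section names the principal investigator and the enrollment and assessment team; it does not say whether operating surgeons knew the allocation. If terminations differ between arms in number or in kind, both the primary comparison and the secondary failure analysis can shift in either direction.

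**Working it through.** **Step 1. Order of events.**

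| Trigger | Relative to randomization (day after surgery) | Later questionnaires stated? |
|---|---|---|
| Cancelled TKA | Before | Not needed; never randomized |
| Contralateral TKA within six months | After | None stated |
| Surgeon's request | After, if made once the patient is randomized | None stated |
| Patient asks to leave the navigator arm | After | Yes, three and six months |

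**Step 2. Does the absence of further evaluation reach terminated patients?** The sentence is written for withdrawn patients. Three things point to the wider reading: a study completion letter is sent at premature termination; participation counts as complete only if all assessments through six months are done; and an invitation to continue is given to one other group alone. The letter also goes to patients who finish the study, so it is not decisive. The wider reading is the natural one, but it is an inference.

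**Step 3. Inputs for size.** From Sample size and power: a 10-point target difference, described as about half the SD of change, so SD is about 20; 10% expected loss; 345 enrolled. The article gives no termination rate, so there is no figure of its own to reproduce. All rates below are assumptions.

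**Step 4. Shift in the primary difference.** Let q be the terminated share in an arm and D the mean improvement of retained minus terminated patients. Within an arm, the retained mean exceeds the mean of all randomized patients by q × D. Between arms the shift is q_nav × D_nav − q_usual × D_usual, which reduces to (q_nav − q_usual) × D when D is the same in both arms. The sign reverses if the shares are swapped.

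| Assumed shares, one arm vs the other | D = 10 | D = 20 |
|---|---|---|
| 3% vs 3% | 0 | 0 |
| 5% vs 2% | 0.3 | 0.6 |
| 8% vs 3% | 0.5 | 1.0 |
| 10% vs 2% | 0.8 | 1.6 |

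Equal shares give zero only if D is equal too. With 5% terminated in each arm and D differing by 10 points between arms, the shift is 0.05 × 10 = 0.5 points.

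**Step 5. Shift in the failure risk difference.** The same identity applies: the arm imbalance in terminations multiplied by the difference in failure rate between terminated and retained patients. For illustration, assume normal change scores with SD 20 and 20% failure among retained patients (z = −0.842).

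- D = 10 (0.5 SD): failure among terminated patients = Φ(−0.842 + 0.5) = 0.366; difference 0.166. A 2-point imbalance gives 2 × 0.166 = 0.3 percentage points.
- D = 20 (1 SD): Φ(−0.842 + 1) = 0.563; difference 0.363. A 5-point imbalance gives 5 × 0.363 = 1.8 percentage points.

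**Step 6. Power.** 345 × 0.90 = 310.5 patients with outcomes. Losing a further 3% to 10% of the 345 leaves about 300 to 276. For a 10-point difference, SD 20 and two-sided 5% (sidedness is assumed), main-effect power is 0.991 to 0.986. Precision is not the issue; possible bias is.

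**The case against.** The strongest defence is that the article ends participation but nowhere excludes anyone from the analysis. It defines intention to treat as analysis by assigned group, and a terminated patient still has an assigned group, a baseline score and perhaps a three-month score. Handling of a missing six-month score is normally left to the analysis plan, which is not shown. This stands against one tempting inference, that the intention-to-treat analysis cannot be done at all or that terminated patients are removed from it. The documents do not say so. It does not answer the narrower point, because no later method supplies an observed score that the follow-up rule did not ask for.

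A reader might also infer that terminations do depend on arm. Nothing in the article shows this. No text links the navigator to scheduling the other knee, and silence about surgeons' blinding does not establish that they knew the allocation. Dependence is possible, no more.

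The entry exclusion of planned bilateral surgery is a real safeguard. Only contralateral operations not planned at entry can reach the termination rule, so the number may be small, and the higher rates assumed above may be too pessimistic. The pilot-based 10% loss is not broken down by cause and may already include terminations, so it cannot be said to leave them out.

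Finally, an imbalance in terminations might be thought to pass almost in full into the failure risk difference. It would do so only if nearly all terminated patients failed and almost no retained ones did; step 5 gives a much smaller figure.

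**Conclusion.** The point holds in limited form. Two post-randomization events end participation with no stated collection of later questionnaires. On the natural reading, the primary outcome is then missing by design for those patients, and intention to treat with observed six-month outcomes for everyone randomized is out of reach. The follow-up rule and the analysis statement need to be reconciled.

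The likely size is modest: about 0 to 1.6 points against a 10-point target, and roughly 0.3 to 1.8 percentage points for the failure endpoint. Both ranges rest on assumed termination shares and assumed differences between terminated and retained patients; the failure range also assumes normal change scores and 20% failure among retained patients. Main-effect power is hardly touched. The rating is should-fix: the defect concerns the primary outcome and is cheap to remove, but its effect is probably small.

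**What to change.** Separate the end of participation in the intervention from the end of data collection. Mail the three- and six-month questionnaires to every randomized patient, including those with a contralateral TKA or a surgeon-requested termination, unless the patient refuses contact. Analyse them in the assigned arm. Report terminations by arm and reason, and add a sensitivity analysis for contralateral TKA. State that cancelled TKA is a pre-randomization exclusion only. Where collection has already closed, the report by arm and reason and the sensitivity analyses are what remains possible.

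The cost is a short amendment, a few extra mailings and $25 payments, and somewhat noisier WOMAC scores in patients recovering from a second knee operation. If 5% of 300 patients were affected (an assumption), that is 15 patients: at most 30 questionnaires and 30 × $25 = $750 if each return is paid. The mailing route already exists and is used for patients who leave the navigator arm. Navigator calls and clinical care need not change.
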